## 3. Statistical Analyses

### 3.1. Baseline Analyses

Continuous variables will be analyzed with the Wilcoxon rank-sum test. Normally distributed data will be assessed by Student’s *t*-test. Categorical data will be assessed using the Fisher’s exact test or χ^2^ test, and risk estimates will be calculated with the odds ratio and 95% confidence intervals (CIs). Data will be presented by mean (standard deviation), median (interquartile range [IQR]), or number (%). Patients with sedation protocol violations or who had serious cardiovascular accidents or who died in the perioperative period or cases that unavoidably required tracheal intubation or had unperformed examinations will be excluded from the final analysis.

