### 2.2. Recruitment and Eligibility Criteria

A special researcher assesses patient eligibility one day before bronchoscopy. The eligible patient, according to the inclusion and exclusion criteria, who agrees to participate in this study is enrolled and randomly assigned to receive either esketamine/propofol- or sufentanil/propofol-based intravenous sedation. The research is canceled in situations where there are patients with serious cardiovascular accidents or who die in the perioperative period.

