### 2.4. Exclusion Criteria

Less than 18 years old at the time of participation.SpO_2_ less than 90% after preoperative oxygenation.History of depression or taking antidepressants.History of neuropsychiatric disorders or drug abuse.Inability to cooperate with the scale assessment.Abnormal liver and kidney function.History of hyperthyroidism.Serious adverse reactions such as cardiac arrest and cardiopulmonary resuscitation during bronchoscopy.Severe hypertension, intraocular pressure, or intracranial pressure.A history of allergy to the study drugs or to eggs or soybeans.

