### 2.5. Randomization and Blinding

Patients are randomly allocated to the esketamine group or the sufentanil group. A computer-generated randomization schedule is conducted to randomly assign included patients in a 1:1 ratio to reach double-blind treatment with either esketamine or sufentanil. Randomly permuted blocks are used for randomizing and are performed by a trained nurse who specializes in research. The nurse will utilize sealed opaque envelopes to reveal the treatment group on the morning of the operation. Esketamine and sufentanil are both colorless and transparent with 1 mL each. The esketamine or sufentanil is diluted to 10 mL with 0.9% saline by an anesthesia nurse on the day of bronchoscopy. The patients, anesthesiologists, investigators, those assessing the outcomes, and those analyzing the data are blind to the treatment assignment.

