## Figures and Tables

**Figure 1 jcm-11-04587-f001:**
[figure not shown]
Study enrollment. SpO_2_, oxygen saturation; PONV, postoperative nausea and vomiting.

**Table 1 jcm-11-04587-t001:** Flow chart of the study. PACU, postanesthesia care unit; POD, postoperative day; CAM, the Confusion Assessment Method; PONV, postoperative nausea and vomiting. “×” means perfoming in that time.

Items	Visit 1	Visit 2	Visit 3	Visit 4	Visit 5
Time	One day before bronchoscoy	Morning of bronchoscopy	During bronchoscopy	PACU	POD1
Eligiblility screen	×				
Medical history and medication history	×				
Surgery history	×				
Physical examination	×				
Inclusion/exclusion criteria	×	×			
Informed consent		×			
Randomization		×			
Demographics			×	×	
Hemodynamic variables			×	×	
Study drug			×	×	
Outcome indicators			×	×	×
CAM				×	×
Aldrete				×	
PONV				×	×
Adverse events			×	×	×
Patient satisfaction					×

**Table 2 jcm-11-04587-t002:** Definitions of the multiple outcomes included in this study protocol. SpO_2_, oxygen saturation; PONV, postoperative nausea and vomiting.

Outcome	Definition	Instrumental/Tool
Incidence of intraoperative hypoxemia	The rate of SpO_2_ < 90% lasts for 30 s during the bronchoscopy.	SpO_2_
Hemodynamic stability and safety	Cardiovascular adverse events such as hypotension or bradycardia, which will be measured as a change >25% from baseline and/or necessitating an intervention.	Non-invasive blood pressure and electrocardiogram
Awakening time	Time from end of bronchoscopy to Aldrete score of 9.	Aldrete
Severe intraoperative hypoxemia	SpO_2_ < 75% at any time during the bronchoscopy.	SpO_2_
Total duration of intraoperative hypoxemia	Total duration of SpO_2_ < 90% during the bronchoscopy.	SpO_2_
PONV	The severity of PONV (none, mild, moderate, and severe).	Likert scale
Delirium	To evaluation of a patient’s delirium status within 3 days after bronchoscopy.	The Confusion Assessment Method
Adverse events	Accidental or adverse reactions to sedatives that threaten or cause patient injury or discomfort	World SIVA International Sedation Task Force Tool
Patient satisfaction	Patient satisfaction with the procedure experience (very unsatisfied, unsatisfied, satisfied, very satisfied)	Likert scale

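### Section 3.1 removes randomised, treated patients from the final analysis because of events after treatment, so the hypoxemia and safety comparisons can be biased by outcome and by arm

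*Protocol article*

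**What the plan says.** Section 3.1 (Baseline Analyses) names the patients who are left out: "Patients with sedation protocol violations or who had serious cardiovascular accidents or who died in the perioperative period", together with "cases that unavoidably required tracheal intubation or had unperformed examinations will be excluded from the final analysis". The sentence stands under a baseline heading, but it refers to the final analysis, so it governs the primary comparison in Section 3.2 as well.

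Section 2.4 includes among the exclusion criteria "Serious adverse reactions such as cardiac arrest and cardiopulmonary resuscitation during bronchoscopy". Section 2.5 places the unmasking of the allocation before that: "The nurse will utilize sealed opaque envelopes to reveal the treatment group on the morning of the operation".

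Section 2.2 treats some of the same events differently: "The research is canceled in situations where there are patients with serious cardiovascular accidents or who die in the perioperative period".

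Table 2 defines the primary endpoint: "The rate of SpO_2_ < 90% lasts for 30 s during the bronchoscopy". Section 2.10 adds severe hypoxemia (SpO2 below 75%) and cardiovascular adverse events as secondary outcomes. The article describes no all-randomised analysis, and no rule counts the excluded patients as events.

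**The concern.** Protocol violation during sedation, cardiovascular accident, perioperative death and unplanned intubation arise after randomisation, and the study drug may influence them. Removing patients on such grounds means that the remaining groups are no longer those created by randomisation.

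Two features make this more than a formality here. First, some of the events lie close to the endpoint. Section 2.7 sets out an escalation for SpO2 below 90% and says that no tracheal intubation will be added. An intubation that became unavoidable most plausibly means that the escalation failed, and such a patient has very probably met the primary endpoint. Second, the Background argues that esketamine causes less cardiovascular and respiratory depression than the opioid regimen. On the trial's own hypothesis, therefore, these events occur at different rates in the two arms.

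At stake are the primary hypoxemia comparison and the comparative safety outcomes. An arm that loses more of its failures looks better than it was.

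**Working it through.** **Where each exclusion falls in time**

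| Ground for exclusion | Source | When it can occur |
|---|---|---|
| Sedation protocol violation | 3.1 | after allocation, during sedation |
| Serious cardiovascular accident, perioperative death | 3.1 (also 2.2) | after allocation, mostly after study drug |
| Unavoidable intubation | 3.1 | after study drug |
| Arrest or resuscitation during bronchoscopy | 2.4 | after study drug |
| Unperformed examination | 3.1 | may be before any study drug |

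Only the last row can describe a patient with no intraoperative SpO2 at all.

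**The plan's own sample size**

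Inputs from Section 2.11: 64% vs 30%, alpha 5%, power 80%, drop-out 10%. Two-sided testing comes from Section 3.4.

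Unpooled normal formula: n = (1.960 + 0.842)² × [0.64×0.36 + 0.30×0.70] / (0.64 − 0.30)² = 7.849 × 0.4404 / 0.1156 = 29.9, so 30 per arm. Adding 10% gives 30 × 1.10 = 33, the stated figure; 30 / 0.90 = 33.3 gives 34. The point therefore does not rest on a sample-size error.

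**What removals can do**

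Assumption: three patients are removed, about 10% of 33 (3.3). The article gives no expected number and does not tie its drop-out allowance to these events. All removed patients are taken to be hypoxemic. The test is the Pearson chi-square of Section 3.2, without continuity correction. Sufentanil is first.

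| All randomised | After removal | Difference (points) | p |
|---|---|---|---|
| 21/33 vs 10/33 | 18/30 vs 10/33 | 33.3 → 29.7 | 0.007 → 0.018 |
| 21/33 vs 10/33 | 21/33 vs 7/30 | 33.3 → 40.3 | 0.007 → 0.001 |
| 21/33 vs 13/33 | 18/30 vs 13/33 | 24.2 → 20.6 | 0.049 → 0.10 |
| 21/33 vs 14/33 | 21/33 vs 11/30 | 21.2 → 27.0 | 0.084 → 0.032 |
| 21/33 vs 13/33 | 18/30 vs 10/30 | 24.2 → 26.7 | 0.049 → 0.038 |
| 21/33 vs 14/33 | 18/30 vs 11/30 | 21.2 → 23.3 | 0.084 → 0.070 |

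The first two rows are near the pilot rates: the estimate shifts in either direction, but the conclusion stands. Rows three and four assume a smaller observed effect and one-arm removals, and the result crosses 0.05. Rows five and six remove three from each arm, and neither crosses.

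The article does not say whether a continuity correction applies. With one, 21/33 vs 13/33 gives p=0.085, so the borderline moves but the argument is the same.

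**Power**

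By the pooled formula at 64% vs 30%, power is 80.5% with 33 per arm and 76.5% with 30. Keeping treated patients in costs no sample size.

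**The case against.** The other side has several fair points, and most of them limit the size of the problem.

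- A reader might infer that the worst hypoxemia outcomes as a class are deleted. The article does not support that. Section 2.7 has the bronchoscope removed, the patient ventilated and the procedure restarted; those patients stay in. No rule removes a patient for SpO2 below 75%. Only desaturations that end in one of the listed events are lost.
- A reader might take unperformed examinations to mean abandoned ones. The text does not say so. An examination never started has no intraoperative SpO2, and leaving it out is defensible.
- A reader might add the criterion "SpO_2_ less than 90% after preoperative oxygenation" as a further post-randomisation exclusion. Table 1 places the eligibility check and randomisation at the same visit without an order between them. The check also precedes any study drug, so neither drug can have caused its result. It is not outcome-dependent in the sense that matters here.
- A reader might infer that the trial's conclusion will reverse. That needs borderline counts and removals concentrated in one arm.
- Section 2.7 says that all adverse events are recorded, so arrests and deaths are not lost from the safety record. That does not return these patients to the comparative analyses.
- Counting every arrest or death as hypoxemia would turn a measured SpO2 endpoint into a composite that was neither pilot-tested nor powered. That stands, and the fix respects it.
- The cancellation in Section 2.2 may mean the patient's participation, which would agree with Section 3.1. The wording leaves this open.

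None of this justifies removing treated patients because of what happened to them after treatment.

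**Conclusion.** The point holds, and it is a defect in the stated rule rather than a detail left to a fuller document. Section 3.1 excludes randomised, treated patients on post-treatment grounds, and Section 2.4 lists as an eligibility criterion an event that can only happen after allocation. The bias is in the design of the rule; its size and direction are unknown, because they depend on how many patients are removed and from which arm.

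Under the assumed loss of three hypoxemic patients from one arm, near the pilot rates, the estimated difference moves from 33.3 to 29.7 points (sufentanil losses) or to 40.3 points (esketamine losses), and p stays below 0.05. The significance verdict changes only in the assumed tables with a smaller observed effect. The link between intubation and the endpoint is a strong inference from Section 2.7, since the article gives no reason for intubation. Because the rule governs the primary analysis and is cheap to change, it should be corrected before unblinding.

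**What to change.** 1. In Sections 3.1 and 3.2, define the primary analysis as all randomised patients who received study drug, in the arm assigned, using the SpO2 recorded up to any event.
2. Count as hypoxemic those who met SpO2 below 90% for 30 s or were intubated for desaturation.
3. Add a sensitivity analysis that counts arrest or death as events.
4. Keep the present exclusion set only as a labelled per-protocol sensitivity analysis, and report exclusions by arm and reason.
5. Patients whose examination was never started and who received no study drug may be left out, with numbers reported by arm.
6. Move arrest or resuscitation during bronchoscopy from the eligibility list in Section 2.4 to the safety outcomes.
7. Reconcile Section 2.2 with Section 3.1, stating whether the cancellation concerns the patient or the trial.

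The cost is a wording change to four sections, and no extra patients. The small downside is that the estimate includes protocol deviators and may be slightly diluted.

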### 2.7. Anesthetic Management

Bronchoscopy is performed in the outpatient bronchoscopy room. All patients fast from food and water for 8 h before bronchoscopy. Preoxygenation is applied 5 min before anesthesia induction. General anesthesia is performed by anesthesiologists. All patients are monitored by noninvasive blood pressure, electrocardiography, and pulse oximetry and infused with 500 mL NaCl 0.9% at the rate of 250 mL/h. All patients receive oxygen administration (3–6 L/min via a nasal cannula) during the bronchoscopy. After preoxygenation with 100% oxygen, sufentanil (0.2 μg/kg) and propofol (1.5–2.5 mg/kg) are administered during the induction of anesthesia in the sufentanil group or propofol (1.5–2.5 mg/kg) and esketamine (0.2 mg/kg) in the esketamine group. Endoscopic examination starts after the patient has no obvious physical activity and the eyelash reflex has disappeared. Simultaneously, general anesthesia is maintained with propofol at a dose of 4–12 mg kg^−1^ h^−1^. The surgeon injects 5 mL of 2% lidocaine (Tianjin Jinyao Pharmaceutical Co., Tianjin, China) through the tracheoscope into the trachea after the tracheoscope enters the glottis. An amount of 0.5 mg/kg propofol will be added if the swallowing reflex, obvious body motion, or choking response is observed. For patients undergoing transient episodes of SpO_2_ below 90%, high fresh oxygen will be used first to obtain sufficient ventilation and to compensate for airway leaks. If this does not work, we will give the patient mandibular support. If none of these works, we will ask the performer to remove the placed bronchoscope and ventilate the patient for a few minutes until the SpO_2_ rises above 95% and then restart the procedure. In this study, it takes approximately 20 min to perform a bronchoscopy examination, and no additional muscle relaxants or tracheal intubation will be added. Intraoperative vasopressors will be administered to maintain mean arterial blood pressure within 20% of the baseline measurement. Propofol is discontinued at the end of the procedure.

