### 2.9. Primary Objective

The primary endpoint of the study—the effect of esketamine versus sufentanil on the incidence of intraoperative hypoxemia—is the rate of SpO_2_ < 90 lasting for the 30 s during the bronchoscopy.

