### 3.2. Primary Outcome Analysis

The primary outcome of our analysis is the incidence of intraoperative hypoxemia. The comparisons in hypoxemia incidence between the two groups will be evaluated with an χ^2^ test, and 95% CIs will be calculated for the difference in hypoxemia incidence.

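### The stated exclusions remove randomized patients for events after allocation, including intubation, which can result from the hypoxemia being measured

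*Protocol article*

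**What the plan says.** All references are to the protocol article.

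- **Section 3.1 (Baseline Analyses)** lists who leaves the final analysis. The list opens with "Patients with sedation protocol violations or who had serious cardiovascular accidents or who died in the perioperative period" and ends with "cases that unavoidably required tracheal intubation or had unperformed examinations will be excluded from the final analysis".
- **Section 3.2 (Primary Outcome Analysis)** sets the primary test: "The comparisons in hypoxemia incidence between the two groups will be evaluated" by chi-square. It names no other analysis set, and no analysis of all randomized patients appears elsewhere.
- **Section 2.5 (Randomization and Blinding)** fixes the timing: "The nurse will utilize sealed opaque envelopes to reveal the treatment group on the morning of the operation".
- **Section 2.7 (Anesthetic Management)** plans the procedure so that "no additional muscle relaxants or tracheal intubation will be added". It treats SpO2 below 90% in steps: more oxygen, then mandibular support, and then "If none of these works, we will ask the performer to remove the placed bronchoscope and ventilate the patient for a few minutes".
- **Section 2.9 (Primary Objective)** defines the target as "the effect of esketamine versus sufentanil on the incidence of intraoperative hypoxemia", with an event being SpO2 below 90% for 30 seconds during bronchoscopy.
- **Section 2.4 (Exclusion Criteria)** includes "Serious adverse reactions such as cardiac arrest and cardiopulmonary resuscitation during bronchoscopy".

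**The concern.** Randomization makes the arms comparable at allocation. That comparability is lost when patients are removed for something the study drug can influence. Sedation violations, cardiovascular accidents, perioperative deaths and intubations can all occur after allocation, and all could differ by drug.

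Intubation does the most harm because it can lie downstream of the primary outcome. If stepwise rescue fails and the patient has to be intubated, that patient is among the clearest hypoxemia events in the trial, and a likely case of the severe hypoxemia counted in Section 2.10. The rule deletes the event and the patient together.

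The direction cannot be known in advance. If the trial's hypothesis is right and severe hypoxemia is commoner on sufentanil, the exclusion hides part of esketamine's benefit. If intubation is commoner on esketamine, it exaggerates that benefit. Blinding stops staff from excluding patients selectively by arm. It does not stop the drug itself from determining who is intubated.

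Safety is affected too. Section 2.10 compares cardiovascular adverse events between arms, while Section 3.1 takes the most serious of them out of the comparison.

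**Working it through.** **Inputs.** Section 2.11 gives 64% hypoxemia on sufentanil, 30% on esketamine, 33 per arm, 10% drop-out, 5% significance and 80% power. Section 3.4 makes tests two-sided. The document gives no rate for intubation or any other excluded event. The exclusion numbers below (1 to 3 of 33, or 10%, all hypoxemic and all from one arm) are therefore assumptions, chosen as a worst case.

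**The plan's own figure.** With the unpooled normal approximation, n = [0.64×0.36 + 0.30×0.70] × (1.96 + 0.84)² / 0.34² = 29.9, so 30 per arm, and 30 × 1.1 = 33. The stated sample size reproduces. The powers below are exact: binomial outcomes are enumerated and tested with the uncorrected chi-square at two-sided 5%. For 33 v 33 at 64% v 30% this gives 83.6%.

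**Bias with no true effect (64% in both arms).** If k hypoxemic patients are dropped from one arm, the bias is 0.64 − (0.64×33 − k)/(33 − k).

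- k = 1: 1.1 points
- k = 2: 2.3 points
- k = 3: 3.6 points
- 10% of the arm: 0.64 − (0.64 − 0.10)/0.90 = 4.0 points

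With 10% dropped from the esketamine arm (33 v 30 at 64% v 60%), two-sided rejection goes from 5.6% to 6.0%. Within that, false positives favoring esketamine go from 2.8% to 4.8%.

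**Bias at the planned effect (34 points).**

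- 10% dropped from sufentanil only: (0.64 − 0.10)/0.90 = 60%. The difference is 60 − 30 = 30 points. Power for 30 v 33 is 67.1%.
- 10% dropped from esketamine only: (0.30 − 0.10)/0.90 = 22.2%. The difference is 64 − 22.2 = 41.8 points.
- Three typical sufentanil patients dropped instead (30 v 33 at 64% v 30%): no bias, and power is 78.0%.

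The sufentanil-only loss of 83.6 − 67.1 = 16.5 points thus splits into 83.6 − 78.0 = 5.6 points from fewer patients and 78.0 − 67.1 = 10.9 points from selection.

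**Effect on significance** (p-values uncorrected; continuity-corrected in brackets).

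| Sufentanil | Esketamine | p |
|---|---|---|
| 21/33 | 10/33 | 0.007 (0.014) |
| 18/30 | 10/33 | 0.018 (0.034) |
| 21/33 | 7/30 | 0.001 (0.003) |

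Near the planned effect, significance does not change. A selected borderline result can: 18/33 v 10/33 gives p = 0.046 uncorrected, and dropping one hypoxemic sufentanil patient (17/32 v 10/33) gives p = 0.062.

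**The case against.** The strongest objection is about size. The large power loss needs 10% of one arm excluded, all of them hypoxemic, with none lost from the other arm. Patients are ASA I–III, those below 90% SpO2 after preoperative oxygenation are not enrolled, and intubation is not a listed rescue step. That intubation follows hypoxemia is an inference from Section 2.7, not a statement in it. About a third of the power loss is ordinary attrition, for which Section 2.11 allows 10%. If the hypothesis is true, the bias is conservative. All of this stands, and it limits the severity of the point. It does not justify the rule, and the attrition share is itself caused by these exclusions.

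Other objections carry less weight:

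- **The rule sits under a baseline heading.** Its wording covers the final analysis, and nothing overrides it.
- **The analysis set belongs in a separate SAP.** The protocol itself states the choice, so this is not missing detail.
- **Section 2.7 records all adverse events.** Serious events are therefore captured, but Section 3.1 still removes those patients from the comparison of arms.
- **The Section 2.4 criterion might mean an earlier bronchoscopy.** This is possible, since neighboring items concern history. The in-study reading is likelier, because Section 2.2 also speaks of canceling the research after serious cardiovascular accidents or perioperative death.
- **Examinations cancelled before sedation do little harm.** Agreed, and the fix lets those patients stay out.

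**Conclusion.** The concern holds. A stated rule makes the primary comparison depend on events after randomization, at least one of which can be a consequence of the outcome.

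On assumed worst cases, the bias is 1.1 to 4.0 points in either direction with no true effect. At the planned effect, a 10% exclusion from one arm changes the 34-point difference to 30 or 41.8 points. Power falls to 67.1% in the sufentanil-only case. If the excluded patients are typical of their arm, bias is zero. Overall false-positive rates barely move, and conclusions change only near the significance threshold. The number and arm of the exclusions cannot be derived from the document. The change should be made because the rule is wrong in principle and cheap to correct, although it would probably not overturn a result close to the one planned for.

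**What to change.** - **Section 3.1:** define the primary analysis set as all randomized patients who start sedation for bronchoscopy, analyzed in their assigned arm. Include those with protocol violations, intubation, serious cardiovascular events or death, and count hypoxemia observed up to the event. Patients whose examination is cancelled before sedation may stay out.
- **Sensitivity analysis:** keep the present exclusions for a per-protocol analysis only, reporting numbers and reasons by arm.
- **Section 2.4:** delete the criterion for arrest or resuscitation during bronchoscopy and report these events as a safety outcome. Section 2.2 should make clear that stopping the research for such a patient does not remove the data already collected.

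**Cost.** These are wording changes. No patients are added, and SpO2 is already monitored. The downside is slight dilution from keeping true violators. If 10% of esketamine patients are violators who get no benefit, their arm's rate is 0.9×0.30 + 0.1×0.64 = 33.4%. Power is then 75.1% (33 v 33) instead of 78.5% with them excluded (33 v 30 at 64% v 30%), a loss of about 3.3 points before rounding. Propofol top-ups given as Section 2.7 prescribes are not violations and need no special handling.
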